#### Secondary outcomes

To examine the safety of olanzapine administration in PTA patients: Difference between olanzapine and placebo groups’ mean number of AEs (as captured via trial bloodwork, Adverse Events Questionnaire, Simpson-Angus Scale, measures of weight, BP, HR, WC) during PTA.To determine whether olanzapine treatment reduces the number of clinically agitated days during PTA: Difference between olanzapine and placebo groups’ mean number of clinically agitated days (ABS score > 21) during PTA.To determine whether olanzapine treatment alters level of agitation at hospital discharge: Difference between olanzapine and placebo groups’ mean ABS score at discharge, controlling for ABS score at treatment commencement.To determine whether olanzapine treatment alters level of cognition in PTA: Difference between olanzapine and placebo groups’ mean levels of PTA as measured using the WPTAS [44, 45], controlling for WPTAS score at baseline. Mean scores will encompass daily assessments of the WPTAS throughout the treatment period, from first day of treatment until emergence from PTA (defined as the first of three consecutive days on which a score of 12 on the WPTAS is obtained). The WPTAS is commonly used in Australia to assess PTA. Seven items on the WPTAS assess orientation to time, person and place, and five assess anterograde memory (therapist face, name and three picture cards). Good construct validity and inter-rater reliability have been demonstrated [45, 61]. Nurses and clinical neuropsychologists who administer the WPTAS at Epworth HealthCare are trained in its use.To determine whether olanzapine treatment alters PTA duration: Difference between olanzapine and placebo groups’ mean number of days in PTA (from date of injury until emergence from PTA based on three consecutive scores of 12 on the WPTAS).To determine whether olanzapine treatment alters cognitive performance following PTA emergence:

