### Statistical methods

#### Analysis of primary and secondary endpoints

Descriptive statistics will be reported using frequencies and percentages for categorical data. Percentages will be calculated based upon the number of patients for whom data are available. Continuous or dimensional variables will be summarised using means and standard deviations, with medians and interquartile ranges (difference between 25th and 75th percentiles) reported for potentially skewed data such as SF-12 PCS and MCS scores.

For the analysis of the primary endpoint, difference in mean daily ABS scores during PTA between olanzapine and control groups, a mixed model/multilevel regression framework [72], taking into account duration of PTA, will be employed. Although a difference between group means corresponding to a large effect size (0.80 of the pooled group standard deviation) is expected, a clinically significant improvement is defined as a difference in group means of the mean daily ABS scores within PTA equal to at least half a pooled group standard deviation difference, the minimal clinically important difference for improvement in irritable/aggression scale scores in TBI [68]. In regard to secondary endpoints, regression methods appropriate to the type of outcome variable will be employed. Comparison of the two groups on dimensional secondary endpoints such as ABS at discharge and WPTAS scores will be analysed using linear regression or median quantile regression. Median quantile regression, based upon the median and so less affected by very high or very low scores, will be employed for possibly skewed variables, such as SF-12v2 MCS and PCS scores, that may not meet the assumptions of linear regression [73].

Secondary endpoints involving count data including number of days in PTA, number of clinically agitated days, length of stay in hospital, agitation scores on discharge, number of “treatment failures” and number of AEs and other measures of treatment safety will be analysed using regression models for count data (Poisson or negative binomial regression as appropriate; [74]).

All statistical tests will be two-tailed, with alpha or statistical significance level set to *p* < 0.05. 95% confidence intervals will be reported throughout. The number of missing observations will be reported. Analyses will assume intention to treat, with all patients analysed as randomised.

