### Harms

A DSMC has been established. The DSMC is independent of the study team and consists of a psychiatrist (chair), neuropsychiatrist and biostatistician. The DSMC will monitor outcomes and be informed of serious AEs and withdrawals. The DSMC will advise study staff on (1) dose reduction, rechallenge or withdrawal in response to AEs, in consultation with the treating doctors; (2) withdrawal of participants due to escalation of agitation to an unmanageable level, resulting in physical aggression posing threat of harm to staff or property, in consultation with study psychiatrist; and (3) necessity of emergency unblinding in response to an AE. No further DSMC charter exists or is currently planned to be developed. The DSMC will not engage in interim analyses. Should a decision need to be made regarding early trial termination, this decision will be made jointly between study principal investigators and the DSMC.

Potential AEs will be monitored in the following ways:

1. Medical information—Weekly measures of weight, BP, HR and WC will be conducted by nursing staff at baseline, weekly throughout the treatment period and following emergence from PTA. Plans for the collection, laboratory evaluation and storage of blood samples are detailed in the provided (Additional file 1).

2. Blood tests—Blood tests assessing fasting lipids, fasting glucose, HBA1C and creatinine will occur at several time points: at baseline, upon the participant’s first score of 12 on the WPTAS (an early indicator of emergence from PTA), monthly throughout the treatment period and following emergence from PTA. Plans for the collection, laboratory evaluation and storage of blood samples are detailed in the provided Appendix: Biological Specimens.

3. The SAS [49]—This scale will be completed by the participant’s treating physiotherapist at baseline and weekly throughout the treatment period. The SAS is a rating scale for extrapyramidal system disturbance widely used to assess side effects related to antipsychotic drug use. It has well-established psychometric properties [49].

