4. Adverse Events Questionnaire—This questionnaire will prompt reporting of AEs expected due to olanzapine use. This questionnaire will be completed weekly throughout the treatment period by the participant’s treating physician in partnership with study staff. Symptoms assessed will include respiratory issues, lethargy, nausea, vomiting, difficulty swallowing, constipation, urinary retention, dizziness and seizures. Information to be collected includes event description, start date, severity, relatedness to treatment, action with investigational product, expectedness, seriousness, outcome, end date and classification.

Clinically significant changes in these parameters will be recorded as AEs. Adverse events will be tabulated and tracked in a password-protected electronic file. All AEs will be followed to adequate resolution or stabilisation, including those that persist beyond the treatment period. If AEs continue beyond hospital discharge, follow-up will occur via telephone.

The DSMC will be informed of all serious AEs. A decision will be made by the treating doctor in consultation with a study psychiatrist and the DSMC as to whether withdrawal from the study, dose reduction or rechallenge is necessary.

Notification and reporting of AEs will be carried out according to the Australian regulatory, ethics committee and International Conference on Harmonisation Good Clinical Practice guidelines.

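### The only named between-arm safety outcome is a pooled count of judged adverse events, so the serial weight, vital-sign, Simpson-Angus and blood values have no named comparison on their own scale

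*Protocol article*

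**What the plan says.** All references are to the protocol article.

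- **Secondary outcomes, first item (safety).** The outcome is the difference between groups in "mean number of AEs (as captured via trial bloodwork, Adverse Events Questionnaire, Simpson-Angus Scale, measures of weight, BP, HR, WC) during PTA". The measurements appear only as routes by which an AE is captured.
- **Harms, conversion rule.** "Clinically significant changes in these parameters will be recorded as AEs". The article gives no numerical criterion.
- **Harms, schedule.** "Weekly measures of weight, BP, HR and WC will be conducted by nursing staff at baseline, weekly throughout the treatment period", and again after emergence from post-traumatic amnesia (PTA). For the Simpson-Angus Scale: "This scale will be completed by the participant’s treating physiotherapist at baseline and weekly throughout the treatment period". "Blood tests assessing fasting lipids, fasting glucose, HBA1C and creatinine will occur at several time points": baseline, the first Westmead score of 12, monthly on treatment, and after emergence.
- **Analysis of primary and secondary endpoints, general clause.** For secondary endpoints, "regression methods appropriate to the type of outcome variable will be employed".
- **Same section, dimensional endpoints.** "Comparison of the two groups on dimensional secondary endpoints such as ABS at discharge and WPTAS scores will be analysed using linear regression" or median regression. No safety measure is among the examples.
- **Same section, count endpoints.** In a sentence that opens by referring to endpoints involving count data, the "number of AEs and other measures of treatment safety will be analysed using regression models for count data" (Poisson or negative binomial). That list also contains agitation scores at discharge.

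**The concern.** Safety is the first secondary aim, and the Background says that good data on the harms of olanzapine in this setting are lacking. The trial collects continuous or scale-score safety data with a baseline value and repeated follow-up. The named outcome reduces each series to whether someone judged a change clinically significant, then adds that event to unrelated events such as nausea or dizziness.

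A shift in mean weight, glucose, lipids or Simpson-Angus score can be real and barely move such a count. The first secondary aim could then be reported as showing no difference while the trial's own measurements differ between arms. The plan treats comparable efficacy data otherwise: for agitation at discharge and for the Westmead score, the Secondary outcomes section names a between-arm difference in means controlled for the starting value.

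**Working it through.** **1. The plan's own figure.** The Sample size section states 26 per group for a standardised difference of 0.80, power 0.80, two-sided alpha 0.05. For a two-sample t test the noncentrality is d × √(n/2).
- n = 25: 0.8 × √12.5 = 2.83, power 0.791.
- n = 26: 0.8 × √13 = 2.88, power 0.807.

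So 26 per group is reproduced, and 26/(1 − 0.10) = 28.9 gives 29. I use 26 per arm below.

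**2. What must be assumed.** The 0.80 is an agitation effect. The documents give no effect size, SD, threshold or event rate for any safety measure. I therefore take shifts of 0.8 and 0.5 SD in one normally distributed measure, and thresholds crossed by 5%, 10% or 20% of placebo patients.

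**3. Comparing the measured values.** Power is 0.81 at 0.8 SD. At 0.5 SD the noncentrality is 0.5 × √13 = 1.80 and power is 0.42. Adjusting for baseline multiplies the SD by √(1 − ρ²). For an assumed ρ of 0.5 to 0.7, power becomes 0.92 to 0.98 at 0.8 SD and 0.55 to 0.71 at 0.5 SD (normal approximation).

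**4. The same shift counted only if it crosses the threshold.** If a proportion q of placebo patients cross, the active proportion is p = 1 − Φ(z − d), where z is the (1 − q) normal quantile. For q = 0.10 and d = 0.8: z = 1.282 and p = 1 − Φ(0.482) = 0.315. Power by exact enumeration, 26 per arm, two-sided 0.05:

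| Shift | Placebo crossing | Active crossing | Fisher | Uncorrected chi-square | Measured values |
|---|---|---|---|---|---|
| 0.8 SD | 5% | 19.9% | 0.214 | 0.396 | 0.807 |
| 0.8 SD | 10% | 31.5% | 0.365 | 0.516 | 0.807 |
| 0.8 SD | 20% | 48.3% | 0.487 | 0.608 | 0.807 |
| 0.5 SD | 5% | 12.6% | 0.041 | 0.151 | 0.424 |
| 0.5 SD | 10% | 21.7% | 0.123 | 0.223 | 0.424 |
| 0.5 SD | 20% | 36.6% | 0.174 | 0.279 | 0.424 |

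**5. Nearer to the planned analysis: a pooled count.** A simulation (4,000 runs) added threshold crossings on nine monitored items (correlation 0.3) to 1 to 4 other AEs per patient, and tested the log rate ratio with empirical variance. All of these settings are assumptions. For shifts of 0.8 SD, power was about 0.06–0.08 with one item shifted, 0.08–0.15 with two and 0.15–0.44 with four. For 0.5 SD the whole range was 0.05–0.19.

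**6. The count-model list.** Two consecutive paragraphs of the analysis section give agitation at discharge two different models: linear or median regression, then count regression. The count list was therefore drawn too widely, and its reference to other safety measures cannot safely be read as limited to true counts.

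**The case against.** **The wording.** The count sentence opens by confining itself to count data, and an earlier clause promises a method suited to each outcome type. On that reading the other safety measures are simply other counts. This is fair. A reader might infer that the plan would fit Poisson regression to weight or glucose, but the documents do not establish that; the text is ambiguous. The ambiguity does not rescue the plan, because if the phrase covers only counts, the measured values have no named between-arm comparison at all.

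**The statistical analysis plan.** A detailed plan is promised, and summaries of laboratory values and vital signs commonly sit there. It may well contain them. The point rests on what the article fixes: the safety outcome, the rule by which a measurement enters it, and the model. An analysis plan that only follows these inherits the weakness.

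**The size of the loss.** A reader might also infer that the trial discards most of its ability to detect metabolic and motor harm. That is too strong. The raw values are kept, and AEs are recorded with severity, relatedness, seriousness and classification. The 0.8 SD is borrowed from agitation, and a single cut of one measure is not the planned count over weekly and monthly monitoring. In the table, the power kept at 0.8 SD runs from about 26% (0.21/0.81) to 75% (0.61/0.81).

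**The remedy.** Unadjusted, the measured values have only 0.42 power at 0.5 SD, so they too can miss a real shift. Ten independent tests at 0.05 would give at least one false positive with probability 1 − 0.95¹⁰ = 0.40. Observation on treatment ends at PTA emergence, itself a trial outcome, so the number of repeated values may depend on treatment. A mixed model does not remove this. All three reservations stand and shape the fix.

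**Conclusion.** The concern holds in a bounded form. The only named between-arm safety outcome is a count of AEs; the serial measurements enter it only through a judgement of clinical significance; and the analysis section names no comparison of those measurements on their own scale. Its count-model list is loosely drawn and contradicts the preceding paragraph on agitation at discharge.

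The planned safety comparison can therefore lose much of the power in data already collected. How much cannot be derived from the documents. In the single-measure illustration the loss ranges from about a quarter to about three quarters of the available power at 0.8 SD, and from about a third (0.28 against 0.42) to about nine tenths (0.04 against 0.42) at 0.5 SD. The pooled count did worse when only one or two measures shifted, and kept up to roughly half (0.44 against 0.81) when four did. The loss lies in the planned comparison, not in the data, and can be fully repaired.

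**What to change.** 1. Keep the number of AEs as a safety outcome.
2. Restrict the count-model sentence to true counts: delete its reference to other safety measures and to agitation scores at discharge, leaving the latter under linear or median regression as the preceding paragraph has it.
3. Add, as supportive safety outcomes, the baseline-adjusted between-arm differences with 95% confidence intervals in weight, waist circumference, blood pressure, heart rate, Simpson-Angus total, fasting glucose, HbA1c and lipids. Use mixed models for the weekly measures.
4. State that these are read as estimates, without significance claims, and that follow-up length varies with PTA duration and may itself be affected by treatment.

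The cost is some wording and a few more models, settled before unblinding, with no new visits or assays. The price is a longer list of secondary comparisons, and an interpretation that must acknowledge the unequal follow-up.

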### Recruitment

Patients admitted to the Epworth HealthCare ABI Unit are routinely screened for PTA status using the WPTAS on admission. Those deemed to be in PTA have the WPTAS and ABS completed on a daily basis by a clinical neuropsychologist or nurse until they emerge from PTA. Study staff will be alerted to potential participants by ABI ward staff. Potential participants include patients in PTA who are exhibiting clinically significant agitation or thought likely to become agitated (due to factors such as agitation during acute hospitalisation). Due to their confusion and inability to lay down new memories, patients in PTA are not cognitively capable of consent. Recruitment will therefore target the patient’s MTDM. This will follow a two-stage process. Firstly, the study will be introduced to the patient’s MTDM by a member of their treating medical team and verbal consent for contact from study staff will be gained. Rapid consent processes are important to recruitment given the time-limited nature of PTA. The decision to introduce the trial to MTDMs of those patients determined likely to become agitated (rather than only those presently agitated) has been made in an effort to expedite the recruitment process and avoid exclusion of eligible participants. Agitation levels of those patients not presently agitated are monitored by study staff. If consent for contact is obtained and the patient is agitated at any stage during PTA, study staff will then contact the MTDM to carry out study consent procedures.

Participant recruitment commenced in June 2019, with the aim of recruiting participants until June 2022. Given that the full study protocol will have a duration of approximately 3 months, on average, data collection will continue until the end of September 2022. Epworth HealthCare treats more than 110 new patients with TBI annually, of whom 80 are likely to be in PTA on admission. Recent research studying this population within the Epworth HealthCare ABI ward [26] showed that 42.4% of TBI patients exhibited significant agitation according to the ABS whilst in PTA. Therefore, approximately 34 patients in PTA are likely to exhibit clinically significant agitation annually. Allowing for declined consent and ineligibility, we envisage recruitment of our sample over a 41-month period.

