Upon emerging from PTA as judged by a score of 12/12 on the WPTAS on three consecutive days, olanzapine will be tapered at a rate deemed appropriate by study doctors. Dose reduction or rechallenge may be undertaken in the setting of an adverse event (AE). Intervention may also be discontinued in the following circumstances: (1) following 6 months in PTA, (2) withdrawal of MTDM consent, (3) due to medical considerations or (4) escalation of agitation to an unmanageable level, resulting in physical aggression posing threat of harm to staff or property.

To maximise compliance, study staff will regularly check that treatment has been administered as prescribed by reviewing the participant’s medical chart. Study staff will also complete a treatment log, recording whether dosages have been administered, and dosage amount.

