### Rescue medication

In the event that agitation levels escalate to an unmanageable level such that this results in physical aggression posing threat of harm to staff or property, participants may be administered a rescue dose of olanzapine. This decision has been made in the interest of participant retention and to represent such highly agitated patients in the participant pool. Multiple incidents of rescue medication use will prompt consideration of withdrawal from participation by the trial Data Safety Monitoring Committee (DSMC) in consultation with the patient’s treating doctor and study psychiatrist.

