### Blinding

The on-site compounding pharmacy, the independent Epworth HealthCare accredited biostatistician who is responsible for creation of the randomisation schedule and the DSMC will be unblinded to group allocation. Olanzapine and placebo capsules will be as visually identical as possible to facilitate comparability of blinded interventions. Participants, MTDMs, ward staff, study staff and all investigators involved in the study will be blinded to treatment allocation. Unblinding will occur following data collection, once data cleaning has been completed.

Emergency unblinding may occur in response to an AE, where knowledge of treatment is required in order to manage the participant’s condition. This will occur in partnership with the DSMC, who will monitor outcomes and be informed of serious AEs and withdrawals. Any intentional or unintentional breaking of the blind will be reported and explained.

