### Retention

To maximise data collection at 3 months post-discharge, participants and MTDM will be reminded at discharge that they will be contacted in 3 months, and told the approximate date of this contact. If a participant or MTDM fails to respond to attempts at 3-month contact, study staff will make every effort to regain contact (via telephone, email and, if necessary, a letter to their last known mailing address). These contact attempts will be documented. Should the participant continue to be unreachable, he or she will be considered to be lost to follow-up. These participants will not be withdrawn from the study, and existing data will be analysed.

Those participants who are withdrawn from the study before the cessation of PTA will be debriefed upon PTA emergence, and informed consent for the use of previously collected data and continuing data collection on outcome measures will be sought in order to allow for intention-to-treat analysis. There will also be continued recording of symptoms as per AE follow-up, if applicable. Any incidents of non-retention and reason for this will be documented.

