If imputation of missing data is required, the method of imputation will depend on the amount of missing data, its characteristics and whether it is the covariates and/or outcome variables that are missing [75]. Following suggested practice, complete case analysis will be reported along with imputation. Multiple imputation will be undertaken separately for each group, and a sensitivity analysis for the assumptions (i.e. missing completely at random) performed [75]. Full details of the imputation procedure will be reported [76]. Statistical analysis will be conducted by a professional Epworth HealthCare or Epworth HealthCare accredited biostatistician, blinded to group assignment, employing a standard statistical package such as Stata 15 or higher. A detailed Statistical Analysis Plan will be prepared by the biostatistician(s).

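### The missing-data check is framed on missing completely at random, although imputation and the primary mixed model rest on missing at random and the protocol links withdrawal to agitation itself

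*Protocol article*

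**What the plan says.** The missing-data text is in the protocol article, Statistical methods, Analysis of primary and secondary endpoints. Imputation is conditional on need. Its method depends on the amount and character of the missing data. It is done separately by group, and "Following suggested practice, complete case analysis will be reported along with imputation". The assumption named is in the next step: "a sensitivity analysis for the assumptions (i.e. missing completely at random) performed". MAR and MNAR are not mentioned anywhere. A detailed statistical analysis plan is promised.

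The grounds for leaving treatment or the trial are elsewhere:

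- Intervention, randomisation and allocation allows the intervention to be discontinued for "escalation of agitation to an unmanageable level, resulting in physical aggression posing threat of harm to staff or property".
- Rescue medication, which is given for the same kind of escalation, adds: "Multiple incidents of rescue medication use will prompt consideration of withdrawal from participation".
- Harms lists, among the matters on which the DSMC advises, "withdrawal of participants due to escalation of agitation to an unmanageable level".
- Blinding states that "the DSMC will be unblinded to group allocation".

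On keeping the data, Recruitment says that patients in PTA "have the WPTAS and ABS completed on a daily basis" until they emerge. Consent (General aspects) seeks permission, when consent is withdrawn, to go on collecting measures the hospital takes anyway. Retention says that, for patients withdrawn before PTA ends, "informed consent for the use of previously collected data and continuing data collection on outcome measures will be sought", on emergence from PTA and for the sake of the intention-to-treat analysis.

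**The concern.** An assumption check is useful only if it tests the assumption the analysis depends on. A check on MCAR can show that missingness is related to observed data. It cannot show whether unseen ABS scores are worse than the observed scores predict. In this trial the first answer is nearly known in advance, because the protocol's own rules let high agitation end treatment or participation, and the primary outcome is mean daily ABS during PTA. The second question decides whether the imputed and mixed-model results can be trusted, and the check as worded does not ask it.

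If one arm, plausibly placebo, loses more of its most agitated patients and their later scores are not collected, the comparison could be distorted and the planned check would not reveal it. A statistical analysis plan written to match this sentence would inherit the problem.

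**Working it through.** **1. The plan's own figures.** Sample size uses a standardised difference of 0.80, SD 4.1 ABS points, power 0.80, two-sided alpha 0.05 and 10% attrition. A two-sample t-test calculation gives 25.52, rounded up to 26 per arm (power 0.807 at 26). Then 26/(1 − 0.10) = 28.9, so 29 per arm and 58 in all. This reproduces the protocol and is not in dispute. On the ABS scale the design difference is 0.80 × 4.1 = 3.28 points. The protocol's clinically significant difference is half an SD, 0.50 × 4.1 = 2.05 points.

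**2. Each analysis and what it needs.**

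| Analysis | Condition for validity | Plausible here? |
|---|---|---|
| Complete case | In general MCAR, or loss depending only on covariates in the model | No, if agitation drives withdrawal and later scores are lost |
| Multiple imputation | MAR given the variables in the imputation model | Yes, if those include the ABS scores and rescue use before withdrawal |
| Mixed model on daily ABS | MAR given the observed scores, and a correct model | Yes, because ABS is scored daily up to withdrawal |

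MCAR belongs to the first row. For the other two, the departure to test is MNAR.

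**3. A bound on the size.** Suppose a fraction f of one arm is wholly unobserved, with a true mean ABS e points above the rest of that arm. The arm's mean is then understated by f × e. The documents give no expected number of agitation withdrawals and no value for e, so both are assumed:

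- 2 of 29, 4 points: 2/29 × 4 = 0.28
- 3 of 29, 8 points: 3/29 × 8 = 0.83
- 5 of 29, 12 points: 5/29 × 12 = 2.07

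Three of 29 is 10.3%, close to the planned attrition; five of 29 is 17.2%. The middle case is 0.83/3.28 = 25% of the design difference and 0.83/2.05 = 40% of the clinically significant one. All three cases assume that no ABS score from these patients enters the analysis and that the other arm loses nobody. If half of each lost patient's days were seen (assumed), and only the unseen days ran 8 points above what the model predicts, the middle case would be roughly 3/29 × 0.5 × 8 = 0.41.

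**4. Direction, by simulation.** Assumed: 21 days of daily ABS, placebo mean 25, between-patient SD 4.1, daily SD 4, and withdrawal with some probability after a high observed score. The true difference in the simulated sample was 3.19.

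| Withdrawal overall | Complete-case difference | Plain mean of observed days |
|---|---|---|
| 7.6% | 2.83 (−11%) | 3.42 (+7%) |
| 9.4% (placebo 14.2%, olanzapine 4.5%) | 2.64 (−17%) | 3.55 (+11%) |
| 17.2% | 2.40 (−25%) | 3.73 (+17%) |
| 32.5% | 1.86 (−42%) | 4.21 (+32%) |

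The two simple summaries err in opposite directions. A random-intercept mixed model in the same set-up gave 3.35 against a true 3.34 at 12% placebo and 3% olanzapine withdrawal (complete case 2.71), and 3.26 against 3.31 at 29% and 11%. When withdrawal follows a recorded high score, the planned type of primary analysis is almost unbiased. The complete-case analysis is not.

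**The case against.** The strongest reply is that the sentence can be read as putting MCAR to the test, next to a complete-case analysis that does need it. The protocol never says in so many words that imputation assumes MCAR. The text is also conditional and defers to a statistical analysis plan, so the lack of a specified MNAR analysis is not in itself a fault. This stands in part. The point is not the missing detail. It is that the one assumption named is not the one imputation depends on.

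A reader might infer that the primary result will be off by about a quarter of the design difference. The documents do not support that. Patients enter with ABS above 21 and are scored daily, the mixed model uses all those scores, and under MAR it showed almost no bias. The 0.83 figure describes patients who contribute nothing, with an assumed excess of about twice the stated SD (8/4.1 = 1.95).

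A reader might also infer that leaving treatment means leaving the data. It does not. The Intervention section speaks of stopping the intervention, the Consent and Retention sections seek continued collection, and the Discussion presents rescue medication as a means of retaining highly agitated patients. The gap is that this collection depends on permission, which Retention seeks only on emergence from PTA, and that Harms speaks of withdrawing participants.

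Finally, a reader might infer that the unblinded DSMC decides who leaves, or reveals allocation to the ABS raters. The protocol shows only that an independent, unblinded committee advises on individual withdrawals in consultation with the study psychiatrist or treating doctors, and that no further charter exists or is planned. Such influence is possible but not shown.

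**Conclusion.** The concern holds in limited form. The protocol frames its missing-data sensitivity analysis on MCAR, while its imputation and primary model rest on MAR, and its own withdrawal grounds make MCAR implausible for an agitation outcome. Two risks remain: MNAR loss where scores after withdrawal are refused or not collected, and bias in the planned complete-case analysis.

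The size cannot be taken from the documents. With one-sided loss of 2 to 5 of 29 patients, wholly unobserved and 4 to 12 points worse, the affected arm's mean shifts by 0.3 to 2.1 ABS points. Under those inputs this is an upper bound for the primary analysis, which keeps the days before withdrawal. The direction of error in the treatment difference depends on the analysis used. The DSMC's unblinded advice is a secondary matter. The change should be made, but the point does not undermine the primary analysis or the sample size.

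**What to change.** - **Assumption.** State MAR as the basis for multiple imputation and the mixed model. Include observed ABS scores and rescue use in the imputation model.
- **Sensitivity analysis.** Replace the MCAR check with a delta-adjusted (pattern-mixture) analysis. Add increasing amounts to imputed ABS on post-withdrawal days, separately by arm, for example +2, +4 and +8 points, and continue to the tipping point. If the complete-case analysis is kept, label it as valid only under the stronger assumption.
- **Data collection.** State that the daily ABS, which is ward routine during PTA, continues to be recorded for the trial after study treatment stops, unless consent for data is withdrawn. Record stopping treatment and stopping data collection as separate events.
- **Secondary safeguard.** Have the DSMC give individual withdrawal advice masked to allocation, with allocation opened only through the existing emergency unblinding route. Who should be withdrawn, and when, is outside this comment.

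The cost is a few sentences of wording and modest extra analysis. No planned figure changes and the total stays at 58. The one small downside is that masked advice may occasionally need a formal unblinding step.
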